| 1. **Study population**   The study period will be from 1st April 2007 to 31st December 2015.  We will perform all analyses in patients that were eligible for all linkages and fulfil the following:   1. registered at a participating English practice prior to the transfer of identifiers to the trusted third party for matching for at least a year before their entry into the study 2. their practice is deemed to be contributing ‘up-to-standard' (UTS) data at study start date 3. they had a valid identifier for linkage (NHS number for ONS mortality and HES data, postcode for IMD) 4. they had not opted out or dissented from CPRD or the linkage scheme 5. individual record is of ‘acceptable' research quality as verified by the CPRD.   **Cohort 1**: Individuals who were registered with a GP contributing to CPRD between 1st April 2007 and 31st December 2015 and who have a complete record on age, gender and IMD are eligible for inclusion in this study (see *P. Plans for addressing missing data*). Patients must have been registered with their GP for at least one year before entering the study with the exception of children aged less than one year who will be assumed to be born into the Practice. Patients can enter the study late or leave the study early in order to include patients who died within the study period (who might be inherently less healthy). Patients enter the study population on the latest of the following dates: continuous registration with GP for 12 months or 1st April 2007. Where patients registered with their GP after the 1st April 2007, patients enter the cohort after 12 months of continuous registration. Patients exit the cohort on the earliest of the following dates: the date the patient died, the date the patient left the practice, or 31st December 2015.  Subsequent studies are nested within cohort 1 (see Error: Reference source not found):   1. Nested cross-sectional study: Patients within cohort 1 with at least one prescription of an antibiotic 2. Nested cohort studies of specific infection syndromes: Patients within cohort 1 with at least one GP consultation for a specific infection syndrome (respiratory, urinary, skin/soft tissue). For these cohorts, patients will enter the cohort on the day of the consultation for infection. Patients will leave the cohort on the earlier of: 28 days after initial consultation, death, transfer out of practice or 31st December 2015. Patients can enter and exit the cohort more than once. |

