| 1. **Exposures, Health Outcomes§ and Covariates**   **§***Please note:**Summary information on health outcomes (as included on the ISAC application form above) will be published on CPRD’s website as part of its transparency policy*  *Exposure*  Exposures will include i) prescription of an antibiotic ii) GP consultation for suspected infection (see Appendices: Table 1 – Codelist for antibiotics, Table 2 – Codelist categorising indications for antibiotic use and Table 3 – Codelists to identify patients with suspected respiratory tract, urinary tract or skin/soft tissue infection)  *Health Outcomes*  The following outcomes (within 28 days of presentation in primary care) will be separately considered for analysis:   - Re-consultation for the same type of infection (CPRD; see Appendix Table 3) - Re-consultation for a side effect of antibiotic treatment (CPRD; see Appendix Table 4a –side effects of antibiotic treatment) - Complications of infection in primary or secondary care (CPRD and inpatient HES; see Appendices: Table 4b and 4c – complications of infection; depending on the indication) - Admission to Accident & Emergency (HES A&E) - All-cause hospitalisation (inpatient HES) - All-cause mortality (CPRD, HES and ONS)   We will undertake a sensitivity analysis to investigate the impact of excluding outcomes that occur on the same day as the exposure. The impact of different time windows will be explored, informed by a literature review on the natural history of the duration of different infections.  *Covariates*  We will include the following covariates:   - Age (classified as 0-4, 5-17, 18-44, 45-64, 65-84, 85-94 and 95+, years of age inclusive) - Sex (female and male) - Index of Multiple Deprivation (IMD; 1-5) - Co-morbidities (coded as indicator variables based on national guidance from Public Health England3 and feasibility1; see Appendix Table 5 for comorbidity code list)   - Diabetes   - Chronic Kidney Disease (CKD)   - Chronic Obstructive Pulmonary Disease (COPD)   - Asthma - Obesity - Smoking status15 - Season (months or quarters) and year - Ethnicity   We will undertake a sensitivity analysis of the impact of coding co-morbidities as binary indicator variable and as total number of co-morbidities. |

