| 1. **Data/ Statistical Analysis**   *1. Estimate the incidence of i) GP consultations for infection and ii) antibiotic prescriptions*  For every patient in cohort 1, data on all consultations for infection and antibiotic prescriptions occurring within the study period will be extracted. We will estimate the incidence of GP consultations for infection and antibiotic prescriptions. This will be done for all consultations and prescriptions, and then separately for each category of infection and each class of antibiotics, based on chapter 5.1 of the British National Formulary (BNF) (see Appendix Tables 1 & 2). The denominator will be estimated as total person-time contributed by patients in the cohort during the study period. We will use Poisson regression to estimate the adjusted rate of consultation and prescription, taking account of the effect of age, gender, SES, ethnicity, selected co-morbidity, smoking and obesity. Random effects will be included to take account of clustering of observations by practice. Rates will be assessed for overdispersion by additionally fitting a negative binomial model and testing for alpha greater than zero via a likelihood-ratio test. If rates are found to be overdispersed, the negative binomial model will be used instead of a Poisson model. Adjusted rate ratios will be presented with 95%-confidence intervals.  *2. Describe antibiotic prescribing patterns linked to the reason for prescription*  The overall number of antibiotic prescribing episodes will be calculated for each patient individually, counting all recorded prescriptions between 1st April 2007 and 31st December 2015. For each episode, a clinical indication will be ascertained. Read codes for a diagnosis or symptom of infection recorded on the same day as the antibiotic prescription will be assumed to represent an indication for the prescription. Where more than one possible indication within the same type of infection is recorded on the day of prescription, the more granular code will be used. If multiple indications across different types of infection are recorded, the prescription will be labelled as having multiple indications. Conversely, if no infectious indication for a prescription was found, the prescription will be labelled as having no infectious indication and we will look for any non-infectious codes associated with the date of antibiotic prescription. The ten most common indications will be established and compared to the same numbers for the period from 1998-2001.14 This approach will be replicated for each class of antibiotics based on chapter 5.1 of the BNF. Patterns of repeat consultation or prescription during episodes of infection which may be prolonged will be investigated for each antibiotic prescription extracted in objective 1. We will define a new episode as a consultation or prescription recorded at least 28 days after any previous consultation for infection or antibiotic prescription. We will undertake sensitivity analyses to investigate the impact of using different time periods to define an episode. We will also examine the use of regular (prophylactic) antibiotic treatment.  Proportions and appropriate 95%-confidence intervals will be calculated and all results will be stratified by age-group, gender, SES, ethnicity, selected co-morbidity, obesity and smoking status. Descriptive data will be displayed graphically.  *3. Estimate the incidence of adverse outcomes in the following 28 days*  For each of the selected clinical infection syndromes in the nested cohort study, events in CPRD, HES and ONS will be searched for all adverse outcomes of interest (see *M.* Exposures, Health Outcomes§ and Covariates). Crude incidence rates of for each outcome will be calculated for patients who were treated (exposed) and not treated (unexposed) with an antibiotic. The denominator will be estimated as the total person-time contributed by patients at risk of each adverse outcome, taking account of the fact that this will be different for each outcome. For example, exposed and unexposed patients cannot consult General Practice if they have been admitted to hospital and should therefore not contribute to the denominator during this period when estimating rates of GP re-consultation in the 28 days following consultation for infection. A Poisson regression model will be used to estimate adjusted rates of adverse outcomes in each group, controlling for age, gender, socio-economic status, ethnicity, co-morbidity, obesity and smoking status and assessing for interaction between age and co-morbidity. Random effects will be included to take account of clustering of observations by practice. If the outcomes are overdispersed, negative binomial models will be used instead of Poisson models. Adjusted rate ratios will be presented with 95%-confidence intervals.  *4. Estimate the number of patients needed to treat with antibiotics to avoid one infection-related adverse outcome*  For each clinical infection syndrome-related adverse outcome identified in objective 3, the odds of that outcome in the 28 days following consultation for those treated with antibiotics (unexposed) and not treated with antibiotics (exposed) will be estimated using logistic regression. We will calculate adjusted odds ratios for the protective effect of antibiotics, adjusting for age, gender, SES, ethnicity, year/season, co-morbidity and the probability of receiving antibiotic treatment (see *O. Plan for addressing confounding*) and assessing for interactions with age and co-morbidity. We will use mixed models to adjust for clustering at a practice level and to take account of clustering of observations within a patient due to repeat episodes of infection. Where there is a significant effect of antibiotics between treated and untreated patients, the NNT or NNH to prevent one individual from developing an adverse outcome is calculated as *1/(absolute risk difference)*. A significant effect will be defined by a p-value < 0.05 for the coefficients of antibiotic treatment and its interactions. To avoid an arbitrary cut-off point, p-values close to 0.05 will also be assessed but discussed separately. The NNT will then be used to assess the clinical relevance of any significant differences found. Whilst the relative risk reduction (RRR) may be similar, the NNT may be different due to differing background risk. This will be explored.  *5. Develop risk prediction tools to support clinical decision making*  For each cohort (i.e. for each of the clinical syndromes of UTI, RTI and SSTI), we will develop a logistic regression risk model to predict the risk of adverse outcomes if patients are treated versus not treated with antibiotics. Models will be developed on a random sample of 80% of the observations within a cohort, reserving 20% of the data to estimate the model’s predictive performance.  A negative outcome will be defined as the occurrence of any of the following within 28 days following the index consultation: hospital admission for infection or complication; re-consultation for infection; A&E admission; death. Antibiotic treatment will be defined as a prescription of an antibiotic on the day of consultation for clinical syndrome. Risk factors will be selected based on the analyses outlined in objectives 1-4 and broadly grouped into: socio-demographic variables, co-morbidity and clinical presentation. Biologically plausible interactions between risk factors and age and between risk factors and co-morbidities will be examined.  Whereas age and sex will be forced into the model, other risk factors will be added in order of their significance in objective 4. Risk factors will be kept in the model if they improve the predictive performance of the model as defined by model discrimination and model calibration.17 For example, a risk factor will be used in the model if it improves discrimination and/or calibration. If a variable improves discrimination but reduces calibration, it will still be included in the model, but will be omitted if it increases calibration at the cost of discrimination.  Model discrimination, i.e. the model’s ability to correctly identify patients with and without an outcome, will be estimated using the concordance (c) statistic.18 The c statistic represents the probability that between two randomly chosen patients, one with the outcome and one without, the model assigns a higher score to the patient with the outcome. As a second measure, model calibration will be assessed using the Hosmer-Lemeshow test.18 We will additionally assess model calibration graphically for reasons for poor calibration by comparing the mean observed outcome in deciles of predicted risk. In this calibration plot, the intercept indicates the extent to which predictions are systematically too low or too high, while the slope reflects overfitting of the model.  For each model, we will estimate the internal validity of discrimination and calibration estimates using cross-validation with bootstrap subsampling based on 1000 iterations. In a secondary analysis, we will assess model performance in subgroups by age, sex and co-morbidity.  Finally, we will develop a simplified scoring system using the risk factors in the model,17 assigning the total score to a specific absolute risk of adverse outcomes in the 28 days following consultation, comparing outcomes if an individual is treated versus not treated with antibiotics. We will assess the predictive performance of the risk scores using the approaches outlined above. |

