| 1. **Plan for addressing confounding**   In objectives 1-3 the aim is to describe rates and undertake descriptive analyses rather than to make inferences about the effect of antibiotic treatment, which is the purpose of objectives 4 and 5. For this reason the issue of confounding is only relevant to objectives 4 and 5.  Individuals who are at higher risk of complications will be more likely to be prescribed antibiotics by their GP (i.e. confounding by indication), introducing a systematic difference between those who are treated and not treated with antibiotics. In this scenario, untreated cases will be less likely to experience adverse events irrespective of their exposure to antibiotics, tending to underestimate the protective effect of antibiotics. We will use propensity score methods to attempt to adjust for this issue. These methods are increasingly used to mitigate the consequences of non-random allocation of treatment in observational studies by modelling the a priori probability of each patient to receive the treatment.  We will use the treatment propensity scores to perform an inverse probability of treatment weighting to account for baseline differences in treated and untreated participants. This will enable assessment of absolute risk and numbers needed to treat to prevent re-consultation and hospitalisation in different groups.19 Propensity score weighting in effect produces a synthetic sample in which the distribution of measured baseline covariates is independent of treatment assignment. Presentation and analyses of results are very similar to a randomized trial allowing assessment of absolute risk and numbers needed to treat in different groups.  In order to create appropriate propensity scores, we will attempt to capture indicators for severity of disease and patients’ risk of complication, such as prior hospitalisation and immunosuppression. Measures such as vital signs are usually poorly recorded which can hamper efforts to estimate disease severity. To overcome this issue we will use GP prescribing preference as an instrumental variables, as described by Davies et al 2013.20  Besides confounding by indication, a number of further factors might influence prescribing. The decision to prescribe an antibiotic is a complex process, depending on multiple characteristics on the patient and practice level. Patients’ demographic factors, patients’ attitude towards antibiotic prescribing, physicians’ workload, date of consultation and geographic location of the practice have been found to influence physicians’ prescribing decisions.21 The use of further instrumental variables may help to estimate the impact of these factors in our analysis and we will also control for differences in prescribing habits between practices through the application of random effects models taking account of potential correlation within multiple episodes of the same patient and between patients within the same practice.  Acknowledging that differences in practice prescribing do not necessarily constitute actually differing prescribing habits but might instead reflect underlying differences in coding, we will undertake an exploratory analysis to look at variation between practices graphically. Using a novel approach we will visualise variability between multiple data-generating sources (i.e. practices) that was specifically designed and tested for multitype, multivariate and multimodal biomedical data.22,23 Where outlying practices are identified, analysis will be re-run without those practices and results presented with the analysis outlined in *N. Data/ Statistical Analysis*. |

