| 1. **Amendments**   **Adding additional covariates in line with previous literature**  Summary:  We would like to include the following additional covariates:   - - Coronary Heart Disease   - Stroke   - Heart Failure   - Peripheral Arterial Disease   - Liver disease   - Immunosuppression   - Composite (Charlson Comorbidity Index - CCI)   Reasoning:  We originally excluded cardiovascular co-morbidities, liver disease, immunosuppression and the CCI because of insufficient power to detect our main effects of interest, i.e. differences between co-morbidities in the number needed to treat (*N. Data/ Statistical Analysis*, step 4.). While this is still the case, we now believe that we do need to include these variables as covariates in our analysis in order to ensure unbiased results and comparability to results from previous literature1,16. In line with the original protocol, **no** attempt will be made to interpret their effect sizes with regards to the number needed to treat (steps 4.-5.), as sample size calculations have indicated low power.  **Additional analysis of confounding**  Summary:  Preliminary analysis has shown unexpected differences to previously published results. These differences could be due to differences in datasets used, differences in countries analysed, or differences in practices and patients included. We plan to further investigate the reasons for the observed difference to be able to present the findings in context.  Reasoning:  After performing analysis of steps 1. and 2. described in section *N.* Data/ Statistical Analysisand comparing them to previous studies on THIN, we found differences in reported rates of antibiotic prescribing and rates of incidence of infection. The size of these differences was up to 30% and persists even when identical code lists and procedures are used. We are not entirely clear why we see these differences, but they seem unlikely to be chance findings and may be clinically relevant, thus warranting further investigation. All previous studies were performed using UK-wide, primary care-only data. We speculate that differences arose because we limited our sample to England-only, HES-linked data. For example, a recent study suggested that i) there might be differences in antibiotic prescribing behaviour between UK countries, with England having lower rates of prescribing than its neighbours.16 These conclusions are in line with our findings, but alternative explanations exist: ii) there might be differences between practices that agree to link their data to HES and ONS as compared to those who don’t, iii) there might be differences between patients who opt out of linkage as compared to those who don’t, and finally iv) there might be differences in practices that contribute to THIN compared to those that contribute to CPRD. In order to be able to appropriately interpret and use the results of this study, we aim to investigate which of the above hypotheses is the most likely. We will rerun all analysis in steps 1. and 2. (which use only primary care) on all patients in CPRD, using the definitions in *K. Study population* but omitting criteria concerning data linkage (bullet points a., c. and the second half of d.). The results from these calculations will then be used to judge whether the observed differences are due to practices excluded because of their country (i), due to practices excluded because of linkage (ii), due to patients excluded because of linkage (iii), or due to practices which are not in CPRD at all (iv). |

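### 28-day all-cause death is compared between treated and untreated patients at all ages with no named marker of palliative or end-of-life care, so mortality odds ratios and NNTs in the oldest and co-morbid strata could be partly artefact

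*Protocol*

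**What the plan says.** Section M lists "All-cause mortality (CPRD, HES and ONS" among the outcomes that, "within 28 days of presentation in primary care) will be separately considered for analysis". Death is therefore analysed on its own and is not restricted to death from infection. The age covariate covers everyone: "Age (classified as 0-4, 5-17, 18-44, 45-64, 65-84, 85-94 and 95+, years of age inclusive".

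Section K has no exclusion for patients close to death and deliberately keeps in those who die: "Patients can enter the study late or leave the study early in order to include patients who died within the study period".

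In section N, objective 4 models "For each clinical infection syndrome-related adverse outcome identified in objective 3, the odds of that outcome in the 28 days following consultation", with interactions by age and co-morbidity. Where the effect is significant, "the NNT or NNH to prevent one individual from developing an adverse outcome is calculated as" the reciprocal of the absolute risk difference. Objective 5 includes death as one of four components of its composite outcome.

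Section O explains confounding by indication: GPs prescribe more to patients at higher risk, so "untreated cases will be less likely to experience adverse events irrespective of their exposure to antibiotics", and protection tends to be underestimated. It plans inverse probability of treatment weighting, gives prior hospitalisation and immunosuppression as examples of inputs, and offers GP prescribing preference as an instrument because severity is poorly recorded. The Amendments section adds cardiovascular conditions, liver disease, immunosuppression and "Composite (Charlson Comorbidity Index - CCI") as covariates.

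**The concern.** A patient already recognised as dying differs from other patients in two ways at once. The 28-day risk of death is very high whatever the antibiotic does, and the decision whether to prescribe may itself depend on the expected death. Treatment and outcome then share a cause that the listed variables do not name.

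A co-morbidity index records diagnoses. It does not record that a patient is expected to die within weeks or that treatment has been limited. Weighting balances what has been measured, and this has not been listed as measured.

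The group is probably concentrated among the oldest and most co-morbid (an assumption). A distortion there would resemble the difference in protective effect between groups that objective 4 sets out to test. A reader guided by section O could also take an apparent mortality benefit as conservative when part of it might be artefact.

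**Working it through.** **Search of the plan.** The protocol states no figure to reproduce. Sections K, M, N and O, the limitations section and the Amendments were read for any exclusion, covariate, propensity input, stratum or sensitivity analysis that marks palliative or end-of-life status. None was found. The same-day sensitivity analysis in section M would leave later deaths in place.

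**Illustration at age 85+.** All inputs are assumptions, because the documents give no end-of-life share, death risk or treatment rate. There is no true effect on death and no adjustment.

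- Base 28-day death risk in other patients: b = 3%
- Death risk in end-of-life patients: d = 30%
- End-of-life share of episodes in an arm: s
- Arm risk = (1 − s) × b + s × d

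Untreated, s = 5%: 0.95 × 3% + 0.05 × 30% = 4.35%.
Treated, s = 2.5%: 0.975 × 3% + 0.025 × 30% = 3.675%.
Risk difference = 0.675 percentage points; 1/0.00675 = 148.
Odds ratio (OR) = (0.03675/0.96325) / (0.0435/0.9565) = 0.84.

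| Untreated share | Treated share | Untreated risk | Treated risk | Crude OR | NNT or NNH |
|---|---|---|---|---|---|
| 5% | 2.5% | 4.35% | 3.675% | 0.84 | NNT 148 |
| 3% | 2% | 3.81% | 3.54% | 0.93 | NNT 370 |
| 3% | 2.5% | 3.81% | 3.675% | 0.96 | NNT 741 |
| equal | equal | equal | equal | 1.00 | none |
| 2.5% | 5% | 3.675% | 4.35% | 1.19 | NNH 148 |

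**All ages**, with assumed base risk 0.3%, d = 30% and shares 0.3% untreated and 0.15% treated: 0.3891% against 0.34455%, OR 0.885.

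**Second parameterisation, by chance of treatment.** Assume end-of-life patients are 1% of episodes, with death risk 30% against 2% in others, and 60% of others are treated.

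- If 40% of end-of-life patients are treated: treated risk = (0.01 × 0.4 × 0.30 + 0.99 × 0.6 × 0.02) / (0.01 × 0.4 + 0.99 × 0.6) = 2.19%. Untreated risk = (0.01 × 0.6 × 0.30 + 0.99 × 0.4 × 0.02) / (0.01 × 0.6 + 0.99 × 0.4) = 2.42%. OR 0.90, NNT about 434.
- If 80% are treated: OR 1.11, NNH about 432.

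With 100,000 consultations (an assumed number), the first case gives z of about 2.4. A bias of this size could pass the p < 0.05 threshold that leads to an NNT.

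**What marking the group does.** Within each stratum (end-of-life or not) the risk difference in these examples is zero by construction, so no NNT arises once the group is correctly identified and stratified or set aside.

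**The case against.** The strongest reply is that this is one candidate confounder absent from a list the protocol leaves open. Section O gives its propensity inputs as examples, and a marker of expected death would fit its stated purpose of capturing risk. The full list may sit in an SAP or in the code-list appendix, neither of which is shown. This lowers the weight of the point. It does not remove it, because the protocol fixes the covariates in section M, extends them by amendment to avoid bias, and discusses a direction of bias that need not hold for death.

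The planned adjustment also counts. Age, co-morbidity, the CCI, prior hospitalisation and immunosuppression are partial proxies, and a valid instrument could in principle deal with unmeasured end-of-life status. The figures above are crude, so they do not show the bias left after the planned analysis. It also stands that none of these identifies the group and that the plan does not say the instrument will be used for the death NNT. Section O mentions NNTs only for re-consultation and hospitalisation, but the objective 4 wording in section N reaches death.

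A reader might infer stronger claims that the documents do not support:

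- *That section O holds confounding to run in one direction only.* It limits its statement to the severity scenario, words it as a tendency, and then names further influences on prescribing.
- *That the bias is large and left without any control.* Even its sign is unknown, it vanishes when shares are equal, and partial controls are planned.
- *That the detectable odds ratio of 0.975 in section I is a yardstick here.* It was derived for a 2.4% outcome risk in the full respiratory sample. It does not transfer to an 85+ subgroup or to rare death at all ages.
- *That the objective 5 tool is materially distorted.* Death is one of four components, and no effect on the composite has been calculated.

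**Conclusion.** The point holds in a limited form. As written, the plan compares all-cause death between treated and untreated patients at all ages and does not name a marker for a group whose treatment decision and death may share a cause. Mortality odds ratios and NNTs in the oldest age bands and co-morbidity groups could be partly artefact, in a direction that section O does not discuss.

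Under the assumed 85+ inputs, the crude odds ratio with no true effect lies between about 0.84 and 1.19. That range rests on assumed shares and death risks and on no adjustment, so it shows what is possible and is not an estimate. The amendment bars interpreting its added covariates for the NNT, so an NNT by CCI is not at issue. This is a worthwhile, low-cost improvement and does not undermine the design.

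**What to change.** 1. Define a code list for palliative or end-of-life care recorded before the index consultation, and add the marker to the propensity model.
2. Report the objective 4 mortality results with and without the marked episodes.
3. Refit the objective 5 models without those episodes as a sensitivity analysis. A mandatory exclusion would change the population the tool is meant for, which is a separate design choice.
4. State in section O that the direction of confounding may differ by outcome, and that for death it may run either way.

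The cost is one further code list on primary care data already held and a small loss of episodes, mainly in the oldest bands, in the sensitivity analyses. Such codes may be incomplete and may vary between practices, as the limitations section already says of clinical coding generally. The marker would then reduce the bias without removing it, and the report should say so.
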